#### Data Management

2.5.2

All information required by the protocol will be recorded in electronic case report forms (eCRFs). eCRFs will be completed using an Electronic Data Capture system. Designated, trained staff at each study site will be responsible for data entry into the eCRF and the correction of such data when necessary. In the event of discrepant data, the study sponsor will request data clarification from the sites. The eCRFs will be reviewed, electronically signed, and dated by the investigator or a designee. Missing data will not be replaced.

### Outcomes

2.6

#### Primary Outcome

2.6.1

The primary endpoint is survival without ventricular arrhythmia recurrence, defined as the interval between the date of ablation and the date of the first recurrence of ventricular arrhythmia. Ventricular arrhythmia recurrence will be defined as the occurrence of an appropriate therapy delivered by the ICD or the occurrence of sustained VT/VF lasting more than 30 s requiring hospitalization. The occurrence and date of the event will be obtained from ICD interrogation. Patients without recurrence will be censored on the date of the last ICD interrogation.

#### Secondary Outcome

2.6.2

The secondary outcomes are: (i) the number of ventricular arrhythmias requiring ICD treatment or hospitalization; (ii) the percentage of patients with ventricular arrhythmia recurrence at 2 years; (iii) the percentage of patients experiencing an electrical storm at 2 years, defined as the occurrence of at least three appropriate therapies (ATP or shocks) delivered by the ICD within 24 h; (iv) the rate of serious complications related to the procedure at 1 month; (v) procedure duration (from puncture to catheter removal, in minutes) and radiofrequency duration (in minutes); (vi) the number of patients hospitalized for cardiovascular reasons (e.g., heart failure, arrhythmias) at 2 years; (vii) the number of patients requiring a repeat ablation; (viii) the mortality rate at 2 years; (ix) the number of patients with non‐inducibility at the end of the procedure; (x) the percentage of patients who experienced inappropriate therapy at 2 years; (x) the duration of hospitalization postablation (days from ablation to hospital discharge) to assess post‐procedural recovery.

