### Follow‐Up Visit

2.4

The patient will receive a telephone call at 6 and 18 months, and will be seen in a consultation at 1 and 2 years following the procedure. This will allow the medical team to inquire about any hospitalizations and the use of antiarrhythmic medications. Remote monitoring will be used to retrieve any recorded arrhythmic event. In the event of hospitalization or consultation, the center or healthcare professional who manages the patient will be contacted to obtain hospitalization reports and check for the occurrence of ventricular arrhythmia.

After 2 years of follow‐up, patients included in the study with a successful procedure and no recurrence will be followed up remotely until (i) arrhythmia recurrence or at the latest, or (ii) the date of the last visit of the last patient included.

Of note, if a new ablation is required during follow‐up due to arrhythmia recurrence, the choice of approach (endocardial only or combined endo‐epicardial approach) will be left to the discretion of the medical team in charge of the patient.

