#### Sample Size Estimation

2.7.1

In two meta‐analyses investigating ICM patients outcomes after endo‐epicardial ablation, the risk of ventricular arrhythmia recurrence at 2 years was 50% in the ‘endocardial‐only’ group and 26% in the ‘endo‐epicardial’ group (HR = 0.43) [20, 21]. To demonstrate this difference, it is necessary to observe 59 events to ensure 90% power with a two‐sided α risk of 5%. To observe a minimum of 59 events required for analysis, we planned to evaluate 150 patients followed for a period of at least 2 years. After the 2‐year follow‐up, patients will no longer be monitored as part of the study, but the ICDs will be remotely interrogated via telemonitoring for patients with no recurrence until (i) arrhythmia recurrence or at the latest (ii) the date of the last visit of the last patient included.

Of note, the sample size estimation is based on treatment effect derived from a prior meta‐analysis of observational studies. However, we acknowledge that the endocardial ablation strategies varied significantly across the included studies, ranging from targeted ablation of clinical/induced VT to complete scar homogenization. This heterogeneity may have influenced the estimated benefit of a combined endo‐epicardial approach and represents a limitation of the current power calculation.

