#### Statistical Analysis

2.7.2

Statistical analyses will be performed using the biometry unit of the Center of Clinical Investigation of Rennes. Interim analyses will not be performed. Patients randomized and undergoing ablation will be analyzed on a “modified intention‐to‐treat” basis. Only patients with a persistent left intraventricular thrombus that definitely contraindicates ablation will be excluded. The expected exclusion rate is very low ( < 3%) and exclusion is not expected to be dependent on the allocated treatment arm. The clinicopathological criteria at inclusion will be described for all patients as well as for each of the two study arms: (i) qualitative variables will be presented as counts and percentages, and (ii) quantitative variables will be presented as means, standard deviations, quartiles, minimums, and maximums. The normality of the distribution of quantitative variables will also be assessed graphically and/or using the Shapiro‐Wilk test, if necessary. The primary endpoint is a censored variable; therefore, both groups will be compared using the log‐rank test. Secondary endpoints will be analyzed according to the type of variable: (i) quantitative variables will be analyzed using the Student's *t*‐test or the Mann–Whitney test if necessary; (ii) qualitative variables will be analyzed using the Chi‐square test or Fisher's exact test if necessary; (iii) censored variables will be analyzed using the Log‐rank test.

Adjustments may be made in cases with heterogeneity at inclusion. The conditions for applying these tests or models will be verified before their implementation. All the tests will be conducted at a significance level of 5%.

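### The arrhythmia count (secondary outcome i) has no time window, while observation after 24 months depends on recurrence and the implied tests ignore exposure

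*Protocol article*

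**What the plan says.** Protocol article, 2.6.2 Secondary Outcome: item (i) is "the number of ventricular arrhythmias requiring ICD treatment or hospitalization". No period is attached. The next item is "the percentage of patients with ventricular arrhythmia recurrence at 2 years", and electrical storm, cardiovascular hospitalization, mortality and inappropriate therapy are also set at 2 years. Serious complications are set at 1 month. Among the outcomes that accrue during follow-up, only (i) and (vii), repeat ablation, carry no window.

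2.7.2 Statistical Analysis: "Secondary endpoints will be analyzed according to the type of variable". Under that rule "quantitative variables will be analyzed using the Student's" t-test, or the Mann-Whitney test if necessary. No test is named for item (i), and no rate, offset or person-time method is mentioned.

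2.4 Follow-Up Visit: after 2 years, "patients included in the study with a successful procedure and no recurrence will be followed up remotely until (i) arrhythmia recurrence", or at the latest until the last visit of the last patient. 2.7.1 Sample Size Estimation has a similar rule without the condition on procedural success: "the ICDs will be remotely interrogated via telemonitoring for patients with no recurrence until (i) arrhythmia recurrence".

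Table 1 has a column for data collection after 24 months. Its only mark is for remote monitoring of VT/VF episodes.

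**The concern.** A count means little without the period over which it was taken. Here the period can depend on the outcome itself. A patient with a recurrence before month 24 stops contributing at month 24. A recurrence-free patient stays under observation and can add one more event. The arm with fewer recurrences therefore has more patients in the extension and more time in which to add events.

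A t-test or Mann-Whitney test on the raw count does not see this. It also treats a patient who dies event-free at month 3 like one who is event-free for 24 months. What is at stake is the meaning and size of one secondary comparison: it would have no clear time reference, and a real benefit would look smaller than it is.

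**Working it through.** **Plan's own figure.** The stated 59 events (HR 0.43, 90% power, two-sided 5%) reproduce with Schoenfeld's formula: 4 × (1.960 + 1.282)² / (ln 0.43)² = 59.0. This figure belongs to the primary endpoint and is not affected here. The same section supplies the risks used below.

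**Inputs from the article.** Two-year recurrence of 50% (endocardial-only) and 26% (endo-epicardial); 150 patients, 1:1, so 75 per arm; the extension rule of 2.4 and 2.7.1.

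**Assumptions.** Exponential time to first recurrence; uniform accrual over A months, with the study ending 24 months after the last inclusion; no deaths or losses; all procedures successful unless stated. Section 2.1 supports two values of A. Recruitment from October 2023 to October 2028 gives 60 months. A total study duration of 60 months, with 24 months of follow-up for every patient, leaves 36.

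**Observation time.** With λ = −ln(1 − p)/24:

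- events added per patient in the extension: e = (1 − p) × [1 − (1 − exp(−λA))/(λA)]
- mean observation: 24 + e/λ

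λ is 0.02888 per month for p = 0.50 and 0.01255 for p = 0.26.

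| Accrual | Arm | Enter extension | Events added per patient | Mean observation (months) |
|---|---|---|---|---|
| 36 | Endocardial | 50% | 0.189 | 24 + 6.5 = 30.5 |
| 36 | Endo-epicardial | 74% | 0.145 | 24 + 11.5 = 35.5 |
| 60 | Endocardial | 50% | 0.262 | 24 + 9.1 = 33.1 |
| 60 | Endo-epicardial | 74% | 0.220 | 24 + 17.5 = 41.5 |

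Before rounding, the differences are 4.97 months (4.97/30.55 = 16%) and 8.45 months (8.45/33.09 = 26%).

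**Effect on the count.** Counts were simulated with 75 per arm and 3,000 runs. After a first recurrence, further episodes were assumed to occur until month 24 at 1, 3 or 10 times the arm's first-recurrence rate. Ratio of mean counts, endo-epicardial to endocardial:

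| Later-episode multiplier | 24-month count | No window, A = 36 | No window, A = 60 |
|---|---|---|---|
| 1 | 0.44 | 0.51 | 0.55 |
| 3 | 0.35 | 0.41 | 0.45 |
| 10 | 0.27 | 0.31 | 0.33 |

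The first row can be checked by hand, because with multiplier 1 the 24-month mean is 24λ (0.693 and 0.301):

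- 24 months: 0.301/0.693 = 0.43
- A = 36: (0.301 + 0.145)/(0.693 + 0.189) = 0.51
- A = 60: (0.301 + 0.220)/(0.693 + 0.262) = 0.55

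**Error rates.** With 40% recurrence in both arms, equal procedural success and multiplier 3, the two tests rejected in 4.6% to 5.3% of runs. With equal rates but success of 70% versus 90% (assumed, and relevant only under the wording of 2.4), mean observation differed by 1.7 months (A = 36) or 2.4 months (A = 60). Mann-Whitney then rejected in 5.9% and 8.3% of runs.

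**Power.** Under the planned risks, Mann-Whitney power was 0.90 to 0.97 for the 24-month count and 0.96 to just over 0.99 with no window.

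**The case against.** The article describes 2-year follow-up and participation of up to 24 months. Section 2.7.1 says that patients leave study monitoring after 2 years. The remote extension appears beside the event requirement, stops at first recurrence, and suits a time-to-first-event endpoint rather than a repeat count. A 24-month count may well be intended. The test for item (i) is also inferred from a general rule, and a count model for one secondary outcome is often left to the full protocol or SAP.

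Much of this is fair. It does not remove the point, because the later episodes will be in the database, nothing excludes them from item (i), and the article wrote a window into the neighbouring items. The follow-up rule and the tests are both stated; taken together they produce the problem.

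Two stronger readings are tempting, and neither is supported:

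- **That the design builds in unequal exposure and so inflates false positives.** The rule is the same in both arms. Imbalance needs a treatment effect on recurrence or a difference in procedural success. With both equal, type I error stays near 5%.
- **That the named tests lose much power or waste most of the information in the counts.** Any such figure needs a mean count, a dispersion and a mortality that the article does not give, and the ranking of the tests reverses between plausible inputs. The missing window itself did not lower power in the simulation.

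**Conclusion.** The point holds and is minor. Followed as written, outcome (i) is a count with no stated period, with outcome-dependent observation after month 24, and with implied tests that ignore exposure. Under the planned effect, the endo-epicardial arm is observed 5.0 to 8.5 months longer on average, and the bias is mainly toward no difference.

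The observation times rest on exponential recurrence, uniform accrual over 36 or 60 months, and no deaths or losses. The count ratios rest in addition on assumed rates of later episodes. The excess rejection of 5.9% to 8.3% applies only to the assumed gap in procedural success. The sample size and the primary log-rank comparison are untouched.

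**What to change.** 1. Define (i) as the number of qualifying arrhythmias within 24 months of the ablation, and put the same limit on (vii), repeat ablation.
2. Analyse (i) as a rate over observed time up to month 24, for example by negative binomial regression with log observed time as offset, reporting a rate ratio with its 95% CI. This accounts for death or loss before month 24. An offset over total follow-up would not do, because time after month 24 is observed only in recurrence-free patients and ends at their first event.
3. Reconcile 2.4 and 2.7.1 on whether a successful procedure is a condition for the extension.

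The cost is wording, with no new data, patients or visits. There are two downsides. Events after 24 months are not used for these outcomes, although they still count for the primary endpoint. The negative binomial test can also be slightly anticonservative at 75 per arm. In simulations with equal arms, 1,500 runs each and assumed over-dispersed counts, the likelihood ratio test rejected in 4.9% to 5.9% of runs and the Wald test in 6.8%. The likelihood ratio version is therefore the safer choice.

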#### Before Hospital Discharge

2.3.4

Transthoracic echocardiography will be performed on the day after the procedure to ensure the absence of pericardial complications. ICDs will be programmed as recommended by guidelines [22], as follows: (i) VF Zone: ≥ 220 bpm, with high‐energy shocks; program 1 burst of ATP before or during charging; long detection intervals (at least 20) should be programmed; (ii) VT Zone: 10–20 bpm slower than the clinical VT rate if known, potentially separated into VT1 and VT2 zones; at least 3 bursts of ATP before delivering shocks in the VT1 zone, and at least 1 burst in the VT2 zone, followed by high‐energy shocks; long detection intervals should be programmed; (iii) Monitor Zone: recommended at 150–160 bpm (if the VT zone extends below this rate, a Monitor Zone is not necessary); (iv) Base Rate: set at 30–40 bpm unless pacing is indicated; (v) SVT discriminators should be programmed ON. Patients will be discharged 24–48 h after the procedure, provided that there are no complications. Upon discharge, a remote‐monitoring report will be scheduled on a monthly basis.

Management of antiarrhythmic drug therapy postablation will be left to the discretion of the treating physician. However, the study protocol recommends discontinuation of AADs whenever feasible. The use of AADs, including initiation, continuation, or discontinuation, will be systematically recorded during follow‐up to assess their potential impact on study outcomes.

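### Electrical storm is counted in ICD therapies, not separate episodes, so one VT/VF episode that resists its first therapies can meet the definition

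*Protocol article*

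**What the plan says.** Section 2.6.2 (Secondary Outcome), item (iii), is the 2-year percentage of patients with electrical storm, which is "defined as the occurrence of at least three appropriate therapies (ATP or shocks) delivered by the ICD within" a 24-hour window. It gives a unit (appropriate therapies), a threshold (three) and a window (24 h). It does not require the therapies to belong to different arrhythmia episodes, and it does not say how several bursts within one episode are tallied.

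Section 2.3.4 (Before Hospital Discharge) sets the ICD programming. For the VT1 zone it specifies "at least 3 bursts of ATP before delivering shocks in the VT1 zone". For the VT2 zone it specifies "at least 1 burst in the VT2 zone", then shocks. For the VF zone the instruction is "program 1 burst of ATP before or during charging", together with shocks. Splitting the VT zone into VT1 and VT2 is optional.

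Two other definitions help in reading item (iii). Item (i) of the same list is "the number of ventricular arrhythmias requiring ICD treatment or hospitalization", which counts arrhythmias. The primary outcome (section 2.6.1) is met by "the occurrence of an appropriate therapy delivered by the ICD", so one therapy is enough, or by a sustained arrhythmia leading to hospitalization.

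**The concern.** The primary endpoint already registers a patient's first treated arrhythmia. A storm outcome adds something if it shows that arrhythmias came in a cluster. With therapies as the unit, three can accrue within one arrhythmia, because the programming delivers them in sequence until the arrhythmia ends.

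The reported percentage would then mix two kinds of patient: those with several arrhythmias in a day, and those with one arrhythmia that the first therapies did not end. It would also depend on how the device was set, because the zone into which an arrhythmia falls decides how many bursts precede a shock. Two people reading the same ICD log could reach different counts, depending on whether they count bursts or ATP sequences. In an open-label trial a mechanical counting rule is worth having.

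**Working it through.** **The plan's own figure.** The storm outcome has no design figure. The only one stated is for the primary endpoint: "it is necessary to observe 59 events to ensure 90% power" (section 2.7.1), with HR 0.43 and two-sided 5% alpha. The Schoenfeld formula for 1:1 allocation reproduces it:

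- events = 4 × (z for 0.975 + z for 0.90)² / (ln HR)²
- = 4 × (1.960 + 1.282)² / (ln 0.43)²
- = 4 × 10.51 / 0.7123 ≈ 59.0

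Power at 59 events is 0.900. Nothing in this calculation uses the storm definition.

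**Counting therapies in one episode.** The inputs are the threshold of three (2.6.2) and the minimum sequences (2.3.4): three bursts in VT1, one burst in VT2, one burst in VF, each followed by shocks if needed. There are two ways to count:

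- Reading A: each burst and each shock is one therapy.
- Reading B: all ATP within an episode is one therapy, and each shock is one therapy.

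| One episode | Reading A | Reading B |
|---|---|---|
| VT1, ended by burst 1 | 1, not met | 1, not met |
| VT1, ended by burst 2 | 2, not met | 1, not met |
| VT1, three bursts, no shock | 3, **met** | 1, not met |
| VT1, three bursts, one shock | 3 + 1 = 4, **met** | 1 + 1 = 2, not met |
| VT1, three bursts, two shocks | 3 + 2 = 5, **met** | 1 + 2 = 3, **met** |
| VT2 or VF, one burst, no shock | 1, not met | 1, not met |
| VT2 or VF, one burst, one shock | 1 + 1 = 2, not met | 1 + 1 = 2, not met |
| VT2 or VF, one burst, two shocks | 1 + 2 = 3, **met** | 1 + 2 = 3, **met** |

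Three things follow.

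1. Under reading A, a VT1 episode is a storm as soon as the third burst is delivered, with no shock and no second arrhythmia. The condition is that bursts one and two both fail.
2. Reading B removes most of these cases but not all: one episode with failed ATP and two shocks still meets the definition in any zone.
3. The result depends on device settings. Under reading A, an episode ended by its third burst in VT1 counts 3 and is a storm. An episode that fails one burst in VT2 and is ended by one shock counts 2 and is not.

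**Counting episodes instead.** With separate episodes as the unit, every row of the table counts 1 and none reaches three.

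**The case against.** **The text does not say that each burst is a therapy.** Item (iii) names ATP and shocks as types of therapy, and the word for a single burst appears only in the programming section. Counting an ATP sequence once is a possible reading. This stands in part: the VT1 case with no shock depends on reading A. The case of one burst and two shocks does not.

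**A journal article condenses, and tallying rules belong in the full protocol or SAP.** This would answer a complaint that a detail is missing. Here the article states a complete rule with unit, threshold and window, and the rule as stated gives the result shown. The same list counts arrhythmias in item (i), so a reader will take therapies in item (iii) at face value.

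**The idea that a storm is a cluster of separate arrhythmias is not in the document.** That is correct. Sections 2.3.4 and 2.6.2 do not contradict each other, and a sponsor could choose to measure therapy burden. The point is about what the outcome measures when the two sections are applied together.

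**A reader might infer that the comparison between arms is biased, with the endocardial arm inflated more.** The document does not support this. The rule and the programming scheme are the same in both arms. An expectation of more misclassified patients in the endocardial arm only restates the assumed recurrence rates (50% against 26%). Nor is overlap with the primary endpoint the fault: any storm defined by appropriate ICD therapy, including the one proposed here, is a subset of primary events.

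**Conclusion.** The point holds in limited form. As worded, item (iii) can class a single therapy-resistant episode as an electrical storm. It does so for VT1 episodes not ended by two bursts if each burst is counted, and for VT2 or VF episodes given one burst and two shocks on either reading. Episodes ended by the first or second VT1 burst are not affected.

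Its size cannot be computed, because the document gives no ATP success rates and no distribution of episodes by zone. A reader might attempt a figure. Suppose each burst succeeds independently with probability p of 0.5 to 0.7. Then (1 − p)² = 25% to 9% of VT1 episodes would receive a third burst. With 150/2 = 75 patients per arm, the planning rates give 75 × 0.50 = 37.5 and 75 × 0.26 = 19.5 recurring patients. One VT1 episode each would put about 3 to 9 and 2 to 5 patients in the storm category from a single episode. These numbers should not be relied on. The success rates are assumed, and independence is doubtful for bursts acting on the same arrhythmia. Not every recurrence is a VT1 episode, and some patients would also have several episodes in a day and so would not be misclassified.

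Only one secondary outcome is affected. The primary endpoint needs a single therapy, so it, the 59 events and the power are unchanged. The change is still worth making, because it is cheap and settles what the storm percentage means.

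**What to change.** Change the counting unit in item (iii) of section 2.6.2 to at least three separate VT/VF episodes, each receiving appropriate ICD therapy, within 24 h. State the minimum interval that separates two episodes, chosen by the sponsor. Add that several bursts or shocks within one episode count once. Recruitment is under way and the trial is open-label, so date the change and make it before storm data are compared by arm.

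The cost is one line of text. Table 1 already lists remote monitoring of VT/VF episodes, so no new data collection is implied. ICD programming and patient care are unchanged.

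The downside is that fewer storms will be counted, so the comparison will rest on fewer patients. A single episode needing several shocks will no longer qualify. If the sponsor considers such episodes important, they can be reported separately.
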